#### Storage checklist

Changes in the compliance with storage recommendations will be assessed using a checklist completed by the study assistant. This checklist will be a modification of a tool used in the previously mentioned intervention study by Lee et al. (2012) [16] and draws on the same sources listed above. This checklist is completed when the data loggers are set up (t0) and again when the temperature readings are downloaded (t2, t3, t4).

##### Waiting list control group

The control group will consist of practices that have temperature readings outside the target range during baseline data collection. The control group will be monitored via a temperature data logger but will receive access to the e-learning program only after t2. By including a control group, an intervention bias due to the set-up of data loggers is taken into account. The control group is closest to regular everyday care and serves as a baseline to better determine the effectiveness of the intervention.

### Safety issues

All practices will be informed in detail about their vaccine refrigerator temperature. The tailored education and the download material will address the issue of how to deal with temperature breaches. Practices with temperature readings outside the target range will receive additional information after t2. The following safety regulations will be followed:Practices with any temperature beyond the target range will receive detailed information on the date and duration of the incident.They will also receive detailed information recommending that the manufacturer’s hotline(s) be contacted for information on how to deal with vaccines exposed to inadequate temperatures, and if additional vaccinations of patients are required to assure patient immunity.In addition, practices will receive the contact data of the Paul Ehrlich Institute, the Federal German agency responsible for vaccines and appropriate management thereof.

### Data collection procedure

#### Practice recruitment

The study will be performed in a random sample of primary care practices in North Rhine-Westphalia, Germany. The sample will be restricted to practices within a 50-km radius of the University Hospital Essen. To support a systematic recruitment process and ensure detailed documentation of all contact attempts and communications with the practices, we will use a response-tracking database. To achieve a high response rate, we will follow a multi-level approach, consisting of up to three invitation letters and up to five phone calls on different days and at different times. The first phone call with each physician is to ensure the eligibility of practice, that is, vaccines are administered, provide additional study information, schedule an appointment for the first practice visit by the study assistant. In order to allow for a nonparticipant analysis, practices refusing participation will be asked to complete a short questionnaire on their practice characteristics (solo/group practice, number of patients quarterly, number of physicians in practice, number of refrigerators used, and availability of a refrigerator thermometer).

#### Randomization

Based on results of the temperature baseline data collection, practices with temperatures outside the target range will be randomized equally to the two study arms (1:1). The randomization procedure is computer-based through www.random.org. No participant will be informed about the study hypotheses in detail.

#### Sample size estimation

The intervention study will be performed in a sample of 46 primary care practices (23 practices per arm) with suboptimal temperature readings at baseline during a 7-day monitoring period (t0). A sample size of 23 practices per group provides an 80 % power to detect anticipated differences between the groups at a significance level of 0.05 %. We assume that 70 % of the practices in the intervention group will reach the temperature target range at follow-up. This assumption is based on two intervention studies of comparable intensity that observed optimal storage conditions in 83 % and 77 % of previously suboptimal practices, using continuous temperature readings as the outcome [18, 19]. Regarding the control group, we expect that 30 % of practices will reach the temperature target range at follow-up due to a study participation effect because of being exposed to temperature monitoring via data logger. This assumption is based on an intervention study that observed optimal temperature readings in 33 % of the control group at follow-up [18].

Owing to the lack of intervention studies available, the power calculation is based on more conservative assumptions.

As the intervention will only be conducted in practices with suboptimal temperatures, a total of 174 practices will have to be recruited for t0. This is based on the assumption that 33.3 % of refrigerators will be outside the target range (n = 58). This percentage is derived from the abovementioned prospective feasibility study in 17 primary care practices with 21 vaccine refrigerators and similar results reported by Bell et al. (2001), Jeremijenko et al. (1996) and Lewis et al. (2001) [14, 18, 20]. Our calculation takes into account a dropout rate of 20 %. This dropout rate is based on our experience and corresponds to reports from other cluster-randomized trials [24]. Using an adaptive design, baseline temperature measurements for t0 will be stopped as soon as the anticipated total sample of n = 58 is reached.

### Statistical analysis

Descriptive statistics will be used to describe baseline characteristics for both study arms with regard to practice characteristics (single/group, number of physicians/medical assistants in practice, number of patients quarterly, average number of vaccinations daily/per week, age structure of patients), participating physician and practice personnel characteristics (sex, age, years in practice/job, part-time/full-time, job content). The effectiveness will be assessed by comparing the intervention and control group and by intragroup comparison (baseline versus follow-up). We will evaluate the effectiveness based on temperature as the main outcome (within range yes/no) by comparing both groups using the chi-square test. For intergroup analyses, all dichotomous secondary outcomes will be evaluated using chi-square tests for each item. In addition, compliance with storage recommendations will be analyzed on the basis of a sum score calculated across all items by using a t-test. For in-group comparisons, McNemar tests will be calculated for dichotomous outcomes and t-tests for dependent samples for sum scores. Temperature monitoring will be measured on an ordinal level to allow for application of the Mann-Whitney U Test (intergroup comparison) and the Wilcoxon signed rank sum test (intragroup comparison). A *P* value <0.05 will be considered significant. All statistical analyses will be performed using IBM SPSS 22® on Windows.

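### The within-arm McNemar test on the primary outcome can only point to improvement, because eligibility sets the baseline at 0 % in range, yet the plan lists within-arm comparison as a way to assess effectiveness

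*Protocol article*

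**What the plan says.** The Statistical analysis section opens its account of effectiveness with two routes joined by 'and': "The effectiveness will be assessed by comparing the intervention and control group and by intragroup comparison (baseline versus follow-up"). The next sentence gives the between-arm test for the primary outcome: "temperature as the main outcome (within range yes/no) by comparing both groups using the chi-square test". Later in the paragraph the within-arm tests are set: "For in-group comparisons, McNemar tests will be calculated for dichotomous outcomes and t-tests for dependent samples for sum scores". That rule is not limited to secondary outcomes, whereas the between-arm rule for the other dichotomous items is. A single 0.05 threshold applies to all tests, and nothing labels the within-arm tests as descriptive or supportive.

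Eligibility for randomisation rests on the same variable. Under Randomization, "practices with temperatures outside the target range will be randomized equally to the two study arms". Under Waiting list control group, "The control group will consist of practices that have temperature readings outside the target range during baseline data collection". Study design has in-range practices followed separately, and Temperature data logging selects one refrigerator per practice.

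Sample size estimation expects that 30 % of control practices "will reach the temperature target range at follow-up due to a study participation effect because of being exposed to temperature monitoring via data logger", based on 33 % in a prior study's control group.

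**The concern.** McNemar's test asks whether changes in the two directions are equally frequent. Here one direction cannot occur. Every randomised practice is out of range at t0, so there is no practice that could move from in range to out of range, and that cell is empty before any data are collected. The null hypothesis of balanced change is therefore not a meaningful one for this sample.

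Whatever brings practices into range without the e-learning counts as improvement. Two such influences apply to both arms: the logger and participation effect that the protocol itself expects, and regression to the mean after selection on an out-of-range week. The section on the waiting list control group says that the control is there to account for the effect of setting up loggers. A within-arm test discards that control.

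At stake is how a disappointing trial would be reported. A significant within-arm P value for the intervention arm would be likely even if the programme did nothing, and the text lists that comparison among the ways effectiveness is assessed.

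**Working it through.** **Inputs from the protocol**
- 23 practices per arm analysed (46 in total); 58 randomised after allowing for 20 % dropout, so 29 per arm (Sample size estimation).
- In range at follow-up: 70 % intervention and 30 % control; source figure for the control rate 33 % (same section).
- In range at baseline: 0 % in both arms, by eligibility.
- Significance threshold 0.05 (Statistical analysis). Two-sided testing is my assumption, since sidedness is not stated. The sample size section prints the level as 0.05 %, but the sample size is reproduced only with 0.05.

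**Reproducing the plan's own figure**
- Per-arm size for 70 % against 30 %, pooled variance, no continuity correction: [1.96 × √(2 × 0.5 × 0.5) + 0.8416 × √(0.7 × 0.3 + 0.3 × 0.7)]² / 0.4² = (1.386 + 0.545)² / 0.16 = 23.3, rounded up to 24.
- At 23 per arm, power is 79.4 % by the normal approximation and 80.9 % by exact enumeration of the chi-square test. The stated 23 and 80 % are therefore sound.
- Dropout: 46 / 0.8 = 57.5, rounded up to 58, as stated.

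**McNemar with one empty cell**

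Let k be the number of practices in an arm that are in range at t2. All k are out-to-in changes; in-to-out changes are always 0.
- Exact two-sided p = 2 × 0.5^k. For k = 5, p = 0.0625; for k = 6, p = 0.031. Significance needs k ≥ 6.
- With continuity correction the statistic is (k − 1)²/k. For k = 5, p = 0.074; for k = 6, p = 0.041. The threshold is again 6.
- Without correction the statistic is k. For k = 3, p = 0.083; for k = 4, p = 0.046. The threshold is 4.

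At the planned control rate the expected k is 0.30 × 23 = 6.9, already above 6.

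**Probability that an arm without the e-learning is declared improved**

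P(k ≥ threshold), with k binomial:

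| Rate in range at t2 | n = 23, exact (k ≥ 6) | n = 23, uncorrected (k ≥ 4) | n = 29, exact (k ≥ 6) |
|---|---|---|---|
| 20 % | 31 % | 70 % | 54 % |
| 25 % | 53 % | 86 % | 77 % |
| 30 % (protocol) | 73 % | 95 % | 91 % |
| 33 % (cited study) | 82 % | 97 % | 95 % |

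The n = 29 column assumes that no practice drops out. At a 10 % rate and n = 23 the exact figure falls to 2 %.

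**How often the two routes would disagree**

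Take 23 per arm, 30 % in range in both arms (no programme effect) and the uncorrected chi-square test between arms. The probability that the intervention arm's exact McNemar test is significant while the between-arm test shows no significant benefit is 71 %, by enumerating both binomials. With 50 % against 30 % it is also 71 %.

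**The case against.** The strongest reply is that the primary analysis is already between-arm. The sentence directly after the two-route sentence ties effectiveness on temperature to the chi-square test between groups, the sample size is built only on a difference between groups, and the control group is justified as the reference for effectiveness. The McNemar sentence follows the tests for secondary outcomes and does not name temperature. This stands in part: the randomised test is specified and nothing here weakens it. It does not remove the point, because the McNemar rule covers dichotomous outcomes without exception and the primary outcome is one.

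A reader might infer that the plan lets a significant within-arm test replace a failed between-arm test. The documents do not say so. No passage gives the within-arm result precedence; the defect is that it stands beside the randomised comparison with no rank or label.

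A reader might also suspect a seasonal push towards improvement, given the planned January start of recruitment. The documents give no direction for season. Out of range means too cold or too warm, so a warmer follow-up could move readings either way, and recruiting up to 174 practices need not place t2 in one season. The point does not rely on it.

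Finally, the size depends on the control rate: for the exact test at 23 practices, significance stops being the more likely result somewhat below 25 %. That is correct, and the table shows it.

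**Conclusion.** The point holds for the primary outcome. Because selection is on the baseline value of that outcome, the within-arm McNemar test can only point to improvement and cannot separate the e-learning from participation and selection effects. Under the protocol's own 30 % control assumption, an arm without the programme would be declared significantly improved with probability 73 % at 23 practices by the exact test. The figures rest on a 0.05 two-sided level, independent practices, one refrigerator per practice and the stated rates at t2.

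The between-arm chi-square test, its power and the data are unaffected. The argument does not extend to the secondary outcomes: eligibility does not fix their baselines, so a reader should not conclude that every within-arm test in the plan has this structural fault. This is a rule that the article states, not a detail left to an analysis plan, so it should be corrected in the text.

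**What to change.** In Statistical analysis, state that effectiveness on the primary outcome is judged only by the randomised between-arm comparison at t2. Remove the McNemar test for that outcome, and report within-arm change in temperature status descriptively, as n/N with a confidence interval.

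Within-arm analyses of the secondary outcomes, and those at t3 and t4, may stay if they are labelled supportive and not presented as evidence of effectiveness. The restriction to t2 should be worded for the primary outcome alone, because Study design plans t3 and t4 for long-term follow-up and the control group receives the programme after t2.

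The cost is a change of wording. No extra data, practices or visits are needed, and the sample size stays as it is.

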## Background

Immunizations are among the most effective and cost-effective public health strategies worldwide [1]. Adequate vaccine storage is a prerequisite to maintain effectiveness and safety of the vaccines. The maintenance of the vaccine cold chain (2 °C to 8 °C) is of utmost importance to assure vaccine potency [2]. Detailed analyses of vaccine temperature sensitivities documented freezing of vaccines as being more critical than heating, at least in our moderate Western European climate. Modern adsorbed hepatitis B vaccines were documented to be the most sensitive vaccines with a freezing point of -0.5 °C [2]. At this temperature, irreversible precipitates of aluminum-containing adsorbents begin to form, which decrease the potency and can induce local irritation upon injection [2, 3].

In a cross-sectional web-based questionnaire survey, we analyzed vaccination management among a 10 % random sample of primary care physicians from one of Germany’s largest federal states, North Rhine-Westphalia [4] using international recommendations for vaccine storage [5–9]. The survey (n = 211) revealed that 16 % of the primary care physicians have experience with cold chain breaches either as an error or near error; 8 % do not regularly control their storage with regard to vaccine wrapping, vaccine expiration date, and refrigerator temperature; 49 % do not keep a storage temperature log; and 21 % fail to use a separate refrigerator solely for vaccine storage. In a recent feasibility study, we observed that the correct temperature range of 2 to 8 °C was not consistently maintained in seven of 21 (33.3 %) vaccine refrigerators from teaching practices. Refrigerators were outside the target range 10.2 % of the total time, with single refrigerators outside the target range for as much as 66.3 % of the time. These results are in line with studies worldwide, which discuss the following key problems related to vaccine storage: 1) temperatures outside the target range [10, 11], 2) lack of adequate temperature measurement devices [12–14], 3) lack of continuous temperature documentation [4, 12–14], 4) use of inadequate refrigerators [9, 10, 12], 5) lack of separate refrigerators [13–15], 6) inadequate storage practices [2, 12, 14, 15], 7) lack of designated personnel [14], and 8) insufficient staff training and guidance [12, 14, 16–18].

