### Outcomes

*Primary outcome:* The proportion of refrigerators with vaccine vials within the target range (+2 °C to +8 °C) during a 7-day monitoring at 5-minute intervals after 6 months. Temperature inside the target range is chosen as the primary outcome, because it is of utmost importance that nonfreezing vaccines are stored in this temperature range. When absorbed mono- and combination vaccines reach their individual freezing thresholds, their chemical structures irreversibly change. This can lead to increased local reactions and reduced effectiveness. The most sensitive vaccines are hepatitis B vaccines with a freezing threshold of -0.5 °C [2]. A thermal analysis of frequently used types of refrigerators by the US Department of Commerce [22, 23] showed that vaccine vial temperatures vary depending on the refrigerator type, loading density and location of vaccines inside the refrigerator. Typical refrigerators used in German primary care are the types “freezerless” (single refrigerator compartment without a freezer) and “dual zone” (separate compartments for refrigerator and freezer, both with individual doors), both so-called domestic refrigerators. Based on different scenarios, that is, door openings and loading density, temperatures can vary by +/-2.3 °C in the type “freezerless” and by +/-4.5 °C in the type “dual zone” [22, 23]. The maintenance of the temperature range of +2 to +8 °C, as recommended by vaccine manufacturers and public health authorities worldwide, is hence justified and therefore serves as a primary outcome measure.

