Temperatures will be measured via a data logger that is approved by the US Center for Disease Control (CDC), and the same type will be distributed to each practice in order to ensure consistency of temperature readings across locations. Continuous measurements over 7 days are planned for baseline (t0) and continuously thereafter, with follow-ups after 6 months (t2), 1 year (t3) and 18 months (t4). Continuous measurements are preferable to single-point measurements because many practices use nonpurpose built refrigerators (so-called domestic refrigerators). Such refrigerators are known to have temperature cycles that result from their on-/off-construction: using the physical principle of the Carnot cycle, they cool down to a specific temperature, after which the cooling department is shut off until a higher temperature is reached [22, 23]. To analyze such temperature fluctuations, we chose a logging interval of one reading every 5 minutes. Similar logging rates were used in prior studies [12, 14, 17, 19, 20]. The logging period of 7 days ensures that at least one regular working week and one weekend are included. This takes differences in patient flow and refrigerator door openings into account (for example, typically more patients on Mondays).

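### The planned between-arm tests are valid but use no baseline value, although t0 temperature severity and the t0 checklist score are already collected; this costs precision in a trial with about 80 % power

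*Protocol article*

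**What the plan says.** The primary outcome, read at six months, is binary per refrigerator (Outcomes): "The proportion of refrigerators with vaccine vials within the target range (+2 °C to +8 °C) during a 7-day monitoring at 5-minute intervals after 6" (the unit is months). The Statistical analysis section names the between-arm tests. For the primary outcome: "We will evaluate the effectiveness based on temperature as the main outcome (within range yes/no) by comparing both groups using the chi-square test". For the checklist: "compliance with storage recommendations will be analyzed on the basis of a sum score calculated across all items by using a t-test".

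Baseline values enter only the within-arm analyses: "For in-group comparisons, McNemar tests will be calculated for dichotomous outcomes and t-tests for dependent samples for sum scores".

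Both baseline measurements exist before allocation:

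- Temperature: "Continuous measurements over 7 days are planned for baseline (t0) and continuously thereafter" (Outcomes). Allocation follows from these readings.
- Checklist: "This checklist is completed when the data loggers are set up (t0) and again when the temperature readings are downloaded" at the follow-ups (Storage checklist).

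The Randomization section describes 1:1 allocation by computer and mentions no stratification. The Sample size estimation section plans 46 analysed practices, 23 per arm, for 80 % power at 70 % versus 30 %, and 58 practices after allowing for 20 % dropout.

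**The concern.** Every randomised practice is out of range at t0, so the yes/no status at baseline is constant and cannot explain any variation at follow-up. The degree of departure is not constant. In the feasibility study, refrigerators were out of range for 10.2 % of total time, "with single refrigerators outside the target range for as much as" 66.3 % (Background). Each t0 record holds 7 × 24 × 12 = 2,016 readings. If the share of these out of range predicts the result at six months, a comparison that conditions on it is more precise than one that does not. The same holds for the checklist score, where the baseline is the same instrument as the outcome.

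The within-arm tests do not fill this gap, because they do not compare the arms. At stake is precision, and some power, in a small trial sized right at its target.

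**Working it through.** **1. The plan's own figure.** Inputs from Sample size estimation: 70 % versus 30 %, 80 % power. The alpha is taken as 0.05 two-sided. That section prints 0.05 %, but Statistical analysis uses 0.05, and a literal 0.0005 would need 57 per arm and give 20.1 % power at 23.

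- Pooled-variance formula: 24 per arm.
- Power at 23 per arm: 79.4 % by formula; 80.9 % by exact enumeration of the uncorrected chi-square.
- Dropout: 46 / 0.80 = 57.5, so 58. Recruitment: 58 × 3 = 174.

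The plan's 23 per arm is reproduced to within one practice. The trial meets its target without adjustment, but only just.

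**2. Primary outcome with one baseline covariate.** The document gives no correlation between t0 severity and the follow-up result, so a range is assumed. Model: severity X is standard normal, logit(p) = a + bX in each arm, with a chosen so that the marginal rates stay at 70 % and 30 %; 23 per arm; 6,000 simulated trials per row. The adjusted test is the arm coefficient in a linear model of the 0/1 outcome on arm and X, that is, an adjusted risk difference.

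| b (odds ratio per SD) | within-arm r | chi-square, same runs | adjusted | difference |
|---|---|---|---|---|
| 0 (1.0) | 0 | 80.3 % | 78.8 % | -1.5 |
| 0.5 (1.65) | 0.22 | 81.1 % | 81.4 % | +0.3 |
| 1.0 (2.7) | 0.39 | 82.3 % | 85.6 % | +3.3 |
| 1.5 (4.5) | 0.50 | 82.0 % | 90.6 % | +8.6 |
| 2.0 (7.4) | 0.57 | 81.0 % | 92.8 % | +11.9 |

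With the marginal rates fixed, the true chi-square power is 80.9 % in every row. The spread in that column is simulation error, about √(0.81 × 0.19 / 6000) = 0.5 points. Measured against 80.9 %, the gains at r = 0.39 and 0.50 are +4.7 and +9.7. A rerun of the same model with 200,000 trials per row gives differences of -1.3, +0.3, +4.5, +8.7 and +12.1.

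Type I error at 30 % in both arms (4,000 trials per row) is 4.7 to 5.5 % for the linear adjusted test and 5.3 to 6.6 % for a logistic likelihood-ratio test. The latter is slightly liberal at this size.

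**3. Compliance sum score.** ANCOVA on the t0 score multiplies the variance of the arm difference by 1 - r². Take an effect for which the t-test has 80 % power (normal approximation): d = (1.960 + 0.842) × √(2/23) = 2.802 × 0.295 = 0.83. Power with ANCOVA = Φ(2.802 / √(1 - r²) - 1.960).

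| assumed r | 1 - r² | power | t-test size with equal precision under ANCOVA, 23(1 - r²) |
|---|---|---|---|
| 0.3 | 0.91 | 83.6 % | 20.9 per arm |
| 0.5 | 0.75 | 89.9 % | 17.3 per arm |
| 0.7 | 0.51 | 97.5 % | 11.7 per arm |

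The gains are about 4, 10 and 18 points.

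**The case against.** The strongest reply is that nothing here is wrong. Under randomisation both tests hold their error rate, the chi-square fits the binary outcome and the sample size calculation, and the target power is met. That stands: the choice is between a valid test and a more efficient one.

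The second reply is that t0 severity may not be prognostic. The Background reports fluctuations over time in 25 % of practices that started with optimal temperatures, and the Outcomes section attributes variation to refrigerator type, loading and door openings. A refrigerator with a constant offset could be far out of range yet easy to correct; one that cycles just past a limit could be the reverse. A percentage-of-time covariate also pools too cold with too warm. This stands as well. A reader might infer from the 66.3 % maximum that severity strongly predicts the six-month result, but the document gives no correlation, and at r of about 0.2 or below the gain is nil or slightly negative.

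Two further inferences fail. At 23 per arm the standardised baseline difference has standard error √(2/23) = 0.295, so a difference above 0.3 SD has a 31 % chance. That is true of any covariate, the test's error rate already allows for it, and it is not bias. The reduction of the readings to yes/no, and the lack of a supportive analysis of time out of range, concern the choice of outcome or matters commonly left to an analysis plan; this point does not rest on them.

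Finally, the secondary outcome is worded as improvement, so the t-test might be meant for change scores. The section does not say so. Even then ANCOVA has the smaller variance, by the factor (1 - r²) / (2(1 - r)) = (1 + r)/2, which is 0.75 at r = 0.5.

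**Conclusion.** The point holds as a loss of precision that the stated tests make avoidable. It is not a bias, and it does not invalidate the primary analysis.

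The omission itself is certain: the tests are named, and no baseline value enters a between-arm comparison. The size of the loss is uncertain, because it rests on assumed correlations, a normally distributed covariate with a correctly specified effect, and 23 analysed practices per arm. For the primary outcome the range runs from about 1 point of power lost to about 9 to 10 points gained at r = 0.50. For the compliance score it is about 4 to 18 points over r = 0.3 to 0.7. The case is clearest for the score, since baseline and outcome are the same checklist. It is a secondary outcome, however, and the trial is not sized on it.

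**What to change.** In Statistical analysis:

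- **Compliance sum score:** replace the unadjusted t-test by ANCOVA of the follow-up score on arm, with the t0 score as covariate.
- **Primary outcome:** prespecify a risk difference with 95 % confidence interval, adjusted for one t0 severity covariate, for example log(1 + percentage of t0 readings out of range). Use a linear or standardised estimator rather than a logistic likelihood-ratio test. Report the unadjusted chi-square alongside it.
- State the covariate and its functional form before any follow-up data are seen. According to Trial status, recruitment was still planned, so this is possible.

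The cost is analysis wording; no new data or practices are needed. The downside is a model-based estimate that at this size should carry only one covariate, and about 1 point of power lost if severity turns out not to be prognostic.
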